#### Effect evaluation and process evaluation

##### Effects and process evaluation of the hospital based reactivation care program

Corrections will take place by means of 'analysis of covariance' for baseline differences in determinants between the locations that could explain differences in functioning or quality of life. Multiple regression analysis will be administered for various outcome variables such as linear regression for continuous outcomes; logistic regression for dichotomous outcomes; proportional odds regression for orderly outcomes and Cox proportional hazards regression for events that occur over time (such as death). Analysis of outcomes at three and twelve months will take into account dependency of these outcomes within persons. The degree of exposure to integrated, multidisciplinary care within the intervention location (process evaluation) will also be correlated with effect measurements in order to see whether greater exposure leads to greater effects. Regression analysis will trace sub-group effects and an interaction term will be included in the model, between type of hospital and sub group (e.g. elderly at high risk for functional loss in comparison to elderly at relatively lower risk for functional loss).

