The program consists of several important elements: First, it aims to identify elderly persons at risk for functional loss at an early stage after hospital admission (= triage within 48 hours of admission). This will make early implementation of interventions possible, which may prevent functional decline and promote a quick return to independent living as well as preserve quality of life [7,22]. Second, the program consists of a combination of integrated interventions offered by a specialized multidisciplinary reactivation team with geriatric expertise. Based on existing literature, this approach is expected to lead to reductions in fall incidence, improved functioning, reduced length of hospital stay, lower (re)admissions to hospital and nursing homes, improved mental well-being of informal caregivers and higher perceived health and life satisfaction among patients as well as better coordination of treatment and follow up between different health care providers and finally, lower mortality [23-34]. Third, the multidisciplinary team uses Goal Attainment Scaling (GAS) to develop and monitor a personalized treatment plan. The GAS method has been successful in maintaining/improving functioning of elderly patients with complex health issues [35,36] and has been standardized for this population [37]. The GAS method consists of several phases: The multidisciplinary team identifies the baseline status of the patient and determines a goal. Then the team will monitor the development per patient and their informal care system by measuring progress regularly, making it possible to adjust interventions and/or goals when necessary. A final GAS measurement will take place to set up a follow up treatment plan before the patient is discharged to the home environment. The fourth element of the program is the possibility for patients with complex problems to be referred by the multidisciplinary team to a stay at a specialized centre for prevention and reactivation (further referred to in this article as "the reactivation centre" or "the centre"). The centre offers a combination of interventions aimed at improving a patient's ability to live as independently as possible in the home environment by providing extra-intensive thematic reactivation treatment alongside regular provisions. It includes specialized nursing home care, paramedical care, specialized mental health care, and treatment and consultations for primary informal caregivers if needed. Patients stay at the reactivation centre for a maximum of three months, after which the multidisciplinary team will develop an individual care-plan for follow up after discharge. Finally, the program will provide support to patients and their informal caregivers by means of a case manager with geriatric expertise who is involved in all aspects of care throughout the period of hospital stay as well as during the follow up period after hospital discharge (irrespective of a patient's destination after discharge whether this is their independent home, the centre for prevention and recovery, a nursing home or any other setting). The case manager is involved in identifying at risk patients in the hospital, coordinating the individual's care plan, coordinating follow up health care for a patient after discharge (e.g. in cooperation with general practitioner, home care or other first line care providers) and aims to support and motivate the patient in treatment adherence. In addition the case manager monitors a patient's risk factors for functional loss throughout all phases of care and may plan extra treatment if necessary as well as improve the care process where possible. Previous programs focused on case management or follow up care have lead to reductions in hospital admissions, nursing home admissions as well as a reduction in length of hospital stay [38,39]. Furthermore, case management may lead to improved access to health care, increased psychosocial support and improved communication with health professionals as valued by patients and their informal caregivers [40].

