#### Inclusion criteria

• patients aged 65 years or older

• admitted in one of the participating hospitals and staying >48 hours

• at risk for functional loss (ISAR HP ≥ 1)

Additional criteria for a stay at the centre for prevention and recovery

• ISAR HP ≥ 2 and/or MMSE ≤ 27 and/or NPI ≥ 3

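### The planned exposure-outcome correlation within the intervention hospital can be confounded by indication, because the program lets care respond to need; it should be adjusted and reported as associational

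*Protocol article*

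**What the plan says.** Under the heading on effects and process evaluation of the hospital based reactivation care program, the protocol article takes the degree of exposure to integrated care inside the intervention hospital, which "will also be correlated with effect measurements in order to see whether greater exposure leads to greater effects". It presents this as part of the process evaluation. The adjustment named in the same section is analysis of covariance "for baseline differences in determinants between the locations that could explain differences in functioning or quality of life".

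The description of the program sets out what determines how much care a patient gets:

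- The team measures progress on Goal Attainment Scaling regularly, "making it possible to adjust interventions and/or goals when necessary".
- The case manager "monitors a patient's risk factors for functional loss throughout all phases of care and may plan extra treatment if necessary".
- The fourth program element is "the possibility for patients with complex problems to be referred by the multidisciplinary team to a stay at a specialized centre".
- The inclusion criteria open the centre to patients with "ISAR HP ≥ 2 and/or MMSE ≤ 27 and/or NPI ≥ 3".

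**The concern.** The sentence fixes a method (correlation) and a causal purpose (whether more exposure produces more effect). Inside one hospital, patients do not receive more or less care at random. Those with worse scores, slower progress or emerging risks can be given more, and the same features predict worse function later. The correlation then mixes any benefit of care with the poorer prognosis of the patients selected for it. A program that works could show a flat or inverse relation, and a reader could take this as evidence that intensive care adds nothing.

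**Working it through.** The article gives no figure for this analysis. Its stated powers (95%, 83%, 95%) belong to the between-hospital comparison. They reproduce as 95.4%, 83.1% and 95.3% at an assumed two-sided 5% level, and do not bear on this point.

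**Step 1: are both links of confounding in the document?**

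- Need to exposure: yes. The program description and the centre criteria, quoted above, let care rise with need both at baseline and during care.
- Need to outcome: yes. The triage section says the ISAR-HP was chosen for factors that predict functional loss. The Background lists cognitive problems and prior functioning among the risk factors.

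**Step 2: does randomisation to the centre break the first link across the hospital?** The plan has about 1100 patients in the intervention hospital. Of these, 200 are allocated to the centre and 200 to no centre after being found eligible. If these 400 are all the eligible patients, 1100 - 400 = 700 are not eligible and none of them goes to the centre. The correlation between eligibility and centre stay is

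(200 × 700 - 200 × 0) / √(400 × 700 × 200 × 900) = 140000 / 224499 = 0.62.

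Randomisation balances the two arms within the eligible group. Across the whole hospital, centre stay still marks higher-risk patients. The figure covers one component of exposure only, and it would be lower if more patients were eligible.

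**Step 3: how much could a crude slope be off?** All values here are assumptions for illustration; none is in the documents. Standardise all variables and code the outcome so that higher is better:

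outcome = b × exposure - g × need + error, with corr(exposure, need) = a.

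The crude slope is b - g × a. It reaches zero when a = b/g.

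| b | g | a = 0.2 | a = 0.4 | a = 0.6 | zero at a |
|---|---|---|---|---|---|
| 0.20 | 0.3 | 0.14 | 0.08 | 0.02 | 0.67 |
| 0.20 | 0.5 | 0.10 | 0.00 | -0.10 | 0.40 |

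With a smaller true benefit, b = 0.10 and g = 0.5, the slope is already 0.10 - 0.5 × 0.2 = 0.00 at a = 0.2.

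**Step 4: how much does baseline adjustment recover?** Let a baseline measure correlate ρ with need and relate to exposure only through need. The adjusted slope is

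b - g × a(1 - ρ²)/(1 - a²ρ²).

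For b = 0.20, g = 0.5, a = 0.6 (crude -0.10):

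- ρ = 0.5: 0.20 - 0.5 × 0.45/0.91 = -0.05
- ρ = 0.7: 0.20 - 0.5 × 0.306/0.8236 = 0.01
- ρ = 0.9: 0.20 - 0.5 × 0.114/0.7084 = 0.12

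Adjustment moves the slope towards 0.20 but does not reach it unless baseline data capture need almost fully.

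**The case against.** The strongest reply is that the section on the centre recognises case mix and treatment regimens as confounders of the program's effects and promises correction, naming diagnoses and clinical treatment data. Its wording concerns the program, so it could be read to extend here. It would therefore be wrong to say that the plan ignores case mix. But the promise stands under the centre heading and does not mention the exposure analysis. Read generously, it covers recorded diagnoses, intake data and baseline characteristics, not need that arises later and prompts extra treatment.

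A second reply is that covariates and exposure metrics are commonly left to a fuller document. That is fair for the detail. It does not answer the stated choice of a correlation for a causal question.

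Third, need is not the only driver of care. Extra treatment is a possibility rather than a rule, and referral also depends on capacity and computer allocation. This stands, and it is why the bias is a possibility of unknown size.

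A reader might also infer that early death cuts exposure short and so creates a false dose-response. The documents do not support this as a firm statement, because exposure is not defined as accumulated volume. The evaluation design gives as examples of process indicators which disciplines were involved and how soon treatment began, and these need not grow with survival. Indicators are nevertheless recorded continuously and, in Table 4, after discharge, so the time window should be fixed.

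**Conclusion.** The point holds as a should-fix matter for a secondary analysis. Both links needed for confounding by indication are in the protocol article, and no safeguard is tied to the exposure analysis. A crude correlation may understate, cancel or reverse a true benefit. The range of 0.14 to -0.10 for a true 0.20 rests wholly on assumed values and shows only that moderate links are enough.

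Two stronger readings are not supported. One is that the analysis will show care as harmful: size and sign cannot be found from the documents. The other is that the trial's main conclusions are at risk: the between-hospital comparison and the intention-to-treat centre comparison do not use this correlation, dose-response is not among the stated objectives, and nothing says that it will decide whether the program works.

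**What to change.** - Replace the correlation with a regression of the T1 and T2 outcomes on exposure. Adjust for T0 Katz-15, ISAR-HP, MMSE, NPI, Geriatric Depression Scale and age, all of which are in Tables 1 and 2. Add admission diagnosis from the hospital registries, and elective or acute status where recorded; neither is listed in those tables.
- Measure exposure only over a period that ends before the outcome is assessed. A centre stay may last three months and T1 falls three months after admission, so for T1 count only the part before T1. Do not divide by length of stay, which is itself a study outcome. Do not restrict exposure to the hospital phase, which would drop the centre stay and case management.
- State that the result is associational, because baseline adjustment reduces the bias without removing it.
- Reserve causal reading for the randomised centre versus no-centre contrast, and account there for the changing allocation probabilities described under Randomisation.

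The cost is analysis wording plus linkage to registry data that are mostly collected already. The price is a weaker and less precise dose-response statement.

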##### Effects and process evaluation of the centre for prevention and recovery

A randomised controlled trial will be analyzed according to the "intention to treat" principle. The process evaluation will study which treatments are carried out in exactly which way. Since differences in case mix and treatment regiments that differ from the program can confound the relation between the program and its expected effects, analysis will be corrected for these possible confounders. For example, data regarding diagnoses of elderly at admission and discharge will be collected and quantitative, clinical treatment data is collected during intake which is focused on medical diagnosis in order to correct for differences in treatment regiments. The randomisation leads to balance between arms of the randomised controlled trial in observed and unobserved predictors of functional decline. Important baseline characteristics are taken into account in analyses to correct for imbalance that might occur by coincidence, thereby increasing power.

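### The intention-to-treat analysis of the centre trial is paired with a correction for treatment regimens and discharge diagnoses that is not limited to variables fixed before randomisation

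*Protocol article*

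**What the plan says.** The section *Effects and process evaluation of the centre for prevention and recovery* makes these statements in order:

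- The randomised trial follows the intention-to-treat principle.
- The process evaluation will study how treatments are carried out.
- A reason for adjustment is given, "Since differences in case mix and treatment regiments that differ from the program can confound the relation between the program and its expected effects", followed by the commitment that "analysis will be corrected for these possible confounders".
- By way of example, "data regarding diagnoses of elderly at admission and discharge will be collected", and "clinical treatment data is collected during intake which is focused on medical diagnosis in order to correct for differences in treatment regiments".
- Randomisation balances the arms on measured and unmeasured prognostic factors, and important baseline characteristics will be adjusted for to deal with chance imbalance and gain power.

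The preceding section, on the hospital programme, has its own adjustment rule: analysis of covariance for baseline differences between locations. It adds a process analysis: "The degree of exposure to integrated, multidisciplinary care within the intervention location (process evaluation) will also be correlated with effect measurements".

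**The concern.** Intention to treat estimates the effect of being allocated to a centre stay. Admission diagnosis and other baseline case mix are sound covariates for that estimate. Treatment received after allocation and diagnoses recorded at discharge are different. In a randomised contrast they cannot be confounders, because they do not influence who is allocated to what. They can be consequences of allocation. Adjusting for a consequence can remove part of the effect. It can also introduce bias through unmeasured prognosis, since prognosis influences both how much treatment a patient gets and how the patient fares.

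The correction stands between the intention-to-treat declaration and the sentence on balance between arms, with no label that makes it secondary. An analyst could follow it literally, adjust the main trial estimate for treatment received, and still report the result as intention-to-treat. The centre comparison is the only randomised evidence in the study (*Weaknesses*), so its estimate should not depend on how this paragraph is read.

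**Working it through.** **1. Timeline, from the protocol.**

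- Triage data are gathered in the first 48 hours after admission (*Triage: identification of elderly at risk for functional loss*).
- Eligible patients are randomised after the additional triage step; no time is given (*Population*).
- Included patients stay longer than 48 hours (*Inclusion criteria*).
- The centre stay comes after the hospital stay (*Setting*).
- Allocation is un-blinded (*Blinding*).
- Medication, diagnosis and consult data are taken from medical registries after discharge (*Demographics*). Process information is also collected at discharge, during the intervention and retrospectively (*Data collection*).

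Hospital discharge will therefore normally follow allocation, and discharge diagnoses can be post-allocation variables. The treatment data are said to be collected at intake. They could precede or follow randomisation; the protocol does not say which.

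**2. Two rules side by side.** The sentence on important baseline characteristics is compatible with intention to treat. The correction for regimens and the citation of discharge diagnoses are wider than that, and no sentence reconciles the two.

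**3. Size.** The protocol gives no figure on this point; its power statement concerns the cohort and is not in dispute. The following is an illustration in which every coefficient is assumed.

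Let A be allocation (0/1), M a post-allocation covariate with variance 1 within each arm, and U an unmeasured prognostic factor with variance 1.

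- M = a·A + l·U + error
- Y = t·A + b·M + g·U + error
- Total effect of allocation: t + a·b, fixed at 0.25 SD

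Given A and M, the expected value of U is l·(M − a·A). The coefficient of A after adjusting for M is therefore t − a·l·g, which equals **0.25 − a(b + l·g)**.

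| Assumed b, l, g | a = 0 | a = 0.25 | a = 0.5 |
|---|---|---|---|
| 0.2, 0, 0 | 0.25 | 0.25 − 0.25(0.2) = 0.20 | 0.25 − 0.5(0.2) = 0.15 |
| 0, 0.5, 0.5 | 0.25 | 0.25 − 0.25(0.25) = 0.19 | 0.25 − 0.5(0.25) = 0.125 |
| 0.2, 0.5, 0.5 | 0.25 | 0.25 − 0.25(0.45) = 0.14 | 0.25 − 0.5(0.45) = 0.025 |
| 0, −0.5, 0.5 | 0.25 | 0.25 + 0.25(0.25) = 0.31 | 0.25 + 0.5(0.25) = 0.375 |

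A simulation of 500,000 patients agreed with the first three rows to within about 0.005. The last row is the formula alone; it represents sicker patients receiving more treatment. The table shows two things: there is no bias when allocation does not shift M (a = 0), and when it does, the sign depends on unknown quantities.

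**4. Separate and minor: the exposure analysis in the programme section.** The programme allows extra treatment when monitoring shows a need, so exposure can track poor prognosis. With standardised variables, an assumed true slope of 0.1, a correlation of −0.5 between exposure and good prognosis, and an effect c of prognosis on outcome, the crude association is 0.1 − 0.5c. It is negative whenever c exceeds 0.2 and positive below that.

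**The case against.** The strongest defence is that the paragraph does not mean what a literal reader could take from it. Four arguments support this.

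- **Intake data may be baseline.** The treatment data are tied to intake and to medical diagnosis. This stands, and it is why the fix allows such data when they were recorded before randomisation.
- **The regimens may lie outside the programme.** The text speaks of regimens other than the programme's, and the *Background* separates medical treatment from reactivation care. On that reading the covariate is not the mechanism of the centre. This weakens the argument that the correction removes the effect itself. It does not make later medical treatment a baseline variable.
- **The centre stay follows hospital discharge.** Discharge diagnoses thus precede the randomised component, and bias requires that un-blinded allocation altered hospital care, discharge timing or coding. This stands as a condition. But the effect of allocation starts at randomisation, and a valid main analysis should not rely on that shift being zero.
- **The sentence may be aimed at the programme comparison or the process evaluation.** It refers to the programme's effects and to case mix, which is a between-hospital problem. This is possible. It nevertheless sits under the trial's heading, and the programme section's own rule covers baseline differences only. On either reading the text needs a correction.

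A reader might go further and infer that the trial's analysis is certain to lose the protection of randomisation. The documents do not support that: no randomisation time is given, the treatment data may be baseline, and the target of the correction is unclear. Nor is the exposure correlation the same error. It is a process analysis in the non-randomised part of the study, where the issue is confounding by need.

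**Conclusion.** The point holds as a defect in a stated rule. Under the trial's heading, the protocol joins intention to treat to a correction that can include variables arising after allocation, without limiting it to pre-randomisation data or assigning it to another analysis. If allocation shifts those variables, the adjusted estimate is no longer the effect of allocation. If it does not, nothing is lost.

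The documents do not allow the size to be fixed. Under the assumed coefficients shown, a true effect of 0.25 SD becomes anything from 0.025 to 0.375 for shifts of 0.25 to 0.5 SD. These figures illustrate the mechanism and the unpredictable sign; they do not forecast this trial. The conclusion rests on hospital discharge normally following randomisation, which the stated timeline supports but does not state outright. The exposure correlation is a lesser, separate matter.

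**What to change.** 1. State that covariates in the intention-to-treat estimate are limited to variables fixed before randomisation, for example T0 Katz-15, age, ISAR-HP, MMSE, NPI, admission diagnosis and acute or elective admission. Admit intake treatment data only if recorded before randomisation.
2. Remove discharge diagnoses and post-allocation treatment from that correction. Report them by arm in the process evaluation, or use them in a separately labelled explanatory analysis.
3. Say which analysis the correction for differing regimens serves. If it is the programme comparison, move it there and reconcile it with that section's baseline rule.
4. Separately, adjust the exposure–outcome analysis for T0 severity and label it descriptive.

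The cost is wording in the protocol and analysis plan. No new data are needed, apart from confirming whether intake treatment data were recorded before or after randomisation.
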